# Cardiometabolic, functional, and psychosocial effects of a remotely supervised home-based exercise program in individuals with type 2 diabetes (RED study): study protocol for a randomized clinical trial

**DOI:** 10.1186/s13063-023-07704-3

**Published:** 2023-10-19

**Keywords:** Diabetes mellitus, Exercise, Physical activity, Glycated hemoglobin, Randomized controlled trial

## Abstract

**Background:**

Type 2 diabetes mellitus (T2D) is a serious global health problem, and exercise is considered an essential non-pharmacological tool in T2D prevention and treatment. During periods of social isolation experienced by the COVID-19 pandemic, home-based exercise programs were strongly recommended as a strategy to facilitate exercise practice and reduce the negative impacts of social isolation. Remotely supervised exercise stands out as an easily accessible strategy after the pandemic, as it is a tool that aims to facilitate access to exercise by this population. The purpose of the RED study is to verify the effects of a remotely supervised home-based exercise program compared to a control group on cardiometabolic, functional, and psychosocial outcomes in patients with T2D.

**Methods:**

Participants are randomized into the control group (CG) and the intervention group (IG). Participants allocated to the CG receive recommendations for the practice of physical activity based on information from chapters of the Physical Activity Guide for the Brazilian Population, while the IG will perform a 12-week home-based exercise program supervised remotely by video call. The intervention has a weekly frequency of two sessions per week on non-consecutive days during the first 6 weeks and three sessions per week on non-consecutive days for the remaining 6 weeks. The RED study has HbA1c as the primary outcome, and the participants’ cardiometabolic, functional, and psychosocial parameters are assessed at baseline (week 0) and post-intervention (week 13).

**Discussion:**

Expected results of the proposed study will provide the knowledge base of health professionals and deliver more evidence for a growing area, i.e., home-based exercise and T2D. Additionally, this protocol aims to verify and demonstrate whether this program can be accessible and effective for different health outcomes in patients with T2D.

**Trial registration:**

The RED study protocol was prospectively registered at ClinicalTrials.gov (NCT05362071). Date registered April 6, 2022. https://clinicaltrials.gov/ct2/show/NCT05362071.

**Supplementary Information:**

The online version contains supplementary material available at 10.1186/s13063-023-07704-3.

## Background

Type 2 diabetes mellitus (T2D) is a metabolic disorder characterized by decreased insulin secretion and sensitivity and corresponds to 90% of all cases of diabetes [1]. Currently, just over half a billion people live with diabetes worldwide [2], with an estimate that by 2045, 783 million adults aged between 20 and 79 will be living with diabetes [1]. The diabetic population generally presents multimorbidity [3] and specific micro and macrovascular complications [4]. These complications increase the mortality risk, impairing the quality of life [4], and are associated with a greater likelihood of developing other physical and mental diseases. The treatment of T2D consists of medication use, diet, and physical exercise [5].

For disease control, glycated hemoglobin (HbA1c) is considered the gold standard marker, as it is a chronic measure effective for monitoring glycemic stability long term [6]. The American Diabetes Association (ADA) recommends the determination of HbA1c in patients with diabetes mellitus therapy in order to monitor the glycometabolic state and thus reduce the risk of the disease [5]. HbA1c predicts the risk of developing diabetic complications [7], and a reduction in levels of this marker is associated with a decreased risk of developing complications of the disease [8, 9]. In addition, high HbA1c values increase the risk of dyslipidemia [10, 11] and are also able to predict the development of arterial hypertension [12]. Moreover, there is an 18% increase in the risk of cardiovascular disease for every 1% increase in absolute HbA1c levels [9, 13]. In this context, exercise is considered an essential non-pharmacological tool in preventing and treating T2D, positively impacting HbA1c levels and different health parameters in this population [14–18].

Currently, Brazil is the 6th country in terms of incidence of diabetes in the world, with 15.7 million adults (20–79 years old) with the disease and with an estimated increase in the number of cases to 23.2 million cases in 2045. In this scenario, it is observed that the country has been presenting an increasing number of diagnoses compared to a decade ago, in which, in 2013, it had 11.9 million cases; in addition, it was responsible for 107,760 deaths in 2019, standing out as a serious public health problem [1, 19–21]. Additionally, the COVID-19 pandemic brought an increase in sedentary behavior and a decrease in physical activity levels [22], one of the pillars in the control and prevention of type 2 diabetes [5]. Faced with this scenario in which it is necessary to seek alternative ways to promote health, the practice of exercises through home exercise programs can become an alternative that is easily accessible and beneficial to this population.

In March 2020, the World Health Organization (WHO) declared the COVID-19 pandemic, which has been considered an unprecedented global health emergency. In this context, social distancing measures were recommended to slow the transmission of the virus. Such measures were necessary strategies; however, they resulted in negative consequences for individuals with TD2. Among them, we can mention a reduction in physical activity levels [23], worsening of glycemic [24] and metabolic control [25], impaired quality of life [26], increases in stress and anxiety levels [27], aggravated depressive symptoms [28], and a worsening of sleep quality [29]. In this context, it was necessary to look for alternatives to control T2D and the negative impacts of social isolation, highlighting the use of telehealth programs [30].

Noteworthy, it has to be highlighted that even before the pandemic, several studies corroborated the effects of home-based exercise programs using or supporting technology in individuals with T2D [31, 32], but those protocols were developed without supervision. Literature showed only [33] that verified effects of an exercise program remotely supervised by video conference in this population. Additionally, during periods of social isolation experienced by the COVID-19 pandemic, home-based exercise programs were strongly recommended as a useful strategy to facilitate the practice of exercises [34, 35]. Furthermore, the use of remote interventions will gain an even greater role in the health area, extending to the application of exercise interventions [36, 37]. However, literature is still scarce regarding studies verifying the results of remotely supervised home-based exercise programs in individuals with T2D. In this way, telehealth stands out as a strategy for the pandemic since it is a tool that facilitates or gives easy access to the practice of exercises. Therefore, we intend to evaluate the effects of a remotely supervised home-based exercise program compared with a control group on cardiometabolic, functional, and psychosocial results in patients with T2D.

## Methods

### Study design

The study is a clinical trial, randomized, single-center trial, and superiority trial with two parallel arms, blinded to outcome assessors and data analysts. The intervention consists of 12 weeks of a remotely supervised home-based exercise program in which cardiometabolic, functional, and psychosocial outcomes are analyzed in individuals with T2D. The RED study has a weekly frequency of two sessions per week on non-consecutive days during the first 6 weeks and three sessions per week on non-consecutive days for the remaining 6 weeks. This clinical trial was designed according to the guidelines for randomized clinical trials: Standard Protocol Items: Recommendations for Interventional Trials (SPIRIT) guidelines [38]. An additional file presents a SPIRIT checklist (see Additional File 1). This trial is being conducted at the Physical Education School of the Federal University of Pelotas (Brazil). The RED study protocol was prospectively registered at ClinicalTrials.gov (NCT05362071).

### Participants

The study participants comprise male and female patients with T2D from the city of Pelotas, located in the state of Rio Grande do Sul in the southern region of Brazil. Volunteers included in the sample are selected by recruitment advertisements on social media and basic health units (BHU) of five health districts located in the city. The BHU is the gateway to the Unified Health System (SUS) and offers multidisciplinary care for free. They are composed of Family Health teams that have a physician, nurse, nursing technician, community health agents, dentist, and oral health technician. In addition, the Family Health teams can work together with the support of the teams from the Expanded Centers for Family Health and Primary Care. These centers have professionals from other specialties, such as speech therapist, psychologist, occupational therapist, physiotherapist, pharmacist, nutritionist, and social worker, in accordance with the health demands of that territory.

### Eligibility criteria

Inclusion and exclusion criteria for participants are defined as follows.

### Inclusion criteria

1. Being under medical treatment using oral hypoglycemic agents;2. Female and male patients with type 2 diabetes;3. Aged ≥ 45 years old;4. Not involved with physical exercises for at least three months (the regular practice of exercise was defined as performing any modality of physical training for at least 20 min on two or more days of the week);5. Being semi-literate due to self-completion questionnaires.

### Exclusion criteria

1. Insulin prescription and use;2. History of cardiovascular disease (except drug-controlled high blood pressure);3. Presence of severe autonomic neuropathy, severe peripheral neuropathy or history of foot injuries, proliferative diabetic retinopathy, severe non-proliferative diabetic retinopathy;4. Muscle or joint impairment that precludes performing physical exercises safely;5. Lack of internet access.

### Recruitment

The recruitment period started in May 2022 and was completed in June 2023. Recruitment takes place through disseminating posters in BHU in the city and notes shared on social networks and the local newspaper. Then, patients are contacted by telephone, and complete information about the purpose of the study and a survey on the presence of conditions related to the inclusion criteria are provided. If the participant meets these criteria, he or she is invited to participate in the study.

### Randomization and allocation concealment

Once included in the study, the participant receives an internal number to be de-identified. The randomization sequence is stratified by sex and disease duration (< 5 years or ≥ 5 years) in blocks of different sizes with a 1:1 ratio in the Excel random function. The entire process of randomization and allocation into groups is carried out by an independent researcher not involved with the evaluations and intervention.

### Sample size

The sample calculation was performed using the GPower version 3.9.1.4 program for *F* tests (considering two groups and two measurements), adopting a significance level of *α* = 0.05 and 80% power. Data for sample size calculation were extracted from the study results [32] for the primary outcome of HbA1c (effect size *f* = 0.24), resulting in a total n of 38 subjects. Additionally, twelve individuals (≈ 30%) will be included in the study due to the possibility of sample losses, totaling 50 participants randomized into the two groups.

### Intervention and control procedure

Participants are randomly allocated to the intervention group (IG), which performs a remotely supervised home-based exercise program lasting a total of 12 weeks, or to the control group (CG). The CG receives general recommendations for physical activity. A detailed description of the intervention and control procedure is provided below:

### Remotely supervised exercise program

The remotely supervised home-based exercise program consists of 12 weeks. Sessions are held via video calls via *WhatsApp*, with a maximum of 5 participants per video call. The intervention has a weekly frequency of two sessions per week on non-consecutive days during the first 6 weeks and three sessions per week on non-consecutive days for the remaining 6 weeks. The 12-week exercise intervention consists of four mesocycles, each with 3-week duration. The session structure is maintained during each mesocycle and is changed for progress in the intensity or volume of its main part in the following mesocycle. The session structure consists of 5 min of warm-up, 37–57 min of the main part, in which a combined training program is carried out, and a final 5 min of stretching. Blocks 1 and 2 will consist of three strength exercises with body weight and alternative materials (500 ml plastic bottles with sand) and an aerobic exercise. Between blocks 1 and 2, and later in block 3, participants take a free walk with displacement in their homes’ available space. The aerobic training intensity is based on the Borg 6–20 Perception of Effort (RPE) Scale [39], while the resistance exercises are performed at the usual/fast speed of execution. The training progression is based on the increase in the number of sets, duration of effort, total duration of the session, intensity, frequency, and complexity of exercises. The alternative material (500 ml plastic bottles with sand) is delivered to all study participants on the day of the home visit. An additional file presents the full periodization of the study in more detail (see Additional File 2). Participants were instructed not to engage in any other type of activity involving exercise during the study period.

### Control group

Participants allocated to the CG receive recommendations for the practice of physical activity based on information from chapters of the Physical Activity Guide for the Brazilian Population (2021) [40]. When going through all the assessments carried out at baseline, the CG participants will receive through *WhatsApp* the information that is available in chapters 1, 4, and 5, which address the following topics: “Understanding Physical Activity,” “Physical Activity for Adults,” and “Physical Activity for the Elderly.” When not possible to send via *WhatsApp*, the print booklet is delivered to the participant. At the end of the 12 weeks, the same booklet is made available to the IG participants.

### Criteria for discontinuing study participation

Participants may be discontinued from the study due to withdrawal of participant consent, lack of interest, or willingness to continue. For participants allocated to the IG, participation is interrupted for safety reasons, such as medical advice or disease complication. In addition, muscle or joint injuries or a severe health event during the study precludes participation in intervention sessions.

### Strategies for trial retention

Participants allocated to the IG receive text messages to reinforce the date and time of interventions. We use *WhatsApp* messages to ask about adverse events if an IG participant misses a session. Sending messages is stopped for participants who declare their withdrawal from the study.

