### Outcomes

Study results are assessed at baseline (week 0) and post-intervention (week 13). Outcomes are measured for all randomized participants, regardless of frequency or completion status. Participants who withdraw from the study at any time after randomization are invited to complete the final study assessments (12 weeks after the start of the intervention). Additionally, only the IG participants perform acute capillary blood glucose measurements before and immediately after an exercise session in the initial period of mesocycles 1, 2, and 4.

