### Adherence

For the IG participants, adherence measures are considered attendance and compliance in the intervention. Attendance is monitored through the online session’s frequency recording and treated as the percent of intervention sessions experienced by each participant, given the total number of applied sessions (thirty sessions). Compliance is treated as the percentage of intervention sessions performed without protocol deviations.

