### Harms

The patients are informed that participation in the study involves a minimal probability of risks and discomforts, especially by the professional prescription and conduction of the exercise sessions. The common discomforts in exercise, such as fatigue during and post-exercise, are also explained to patients, which may require reducing the intensity or stopping the exercise. The research team is available to solve any adverse events. If adverse events are reported, they are collected and classified according to severity (i.e., mild, moderate, or severe), predictability (i.e., expected or unexpected), and potential relationship to study procedures (i.e., definitely related, possibly related, or unrelated).

Participants were instructed to take classes whenever possible with a companion at home. Additionally, the person responsible for applying the intervention has a list with the emergency contact telephone number and the address provided by the participants. In case of any more serious adverse event, the person responsible will contact the mobile emergency service, provide the address participant, and immediately inform the emergency contacts. In addition, the participants were instructed regarding care with food, hydration, clothing, and medication for the classes.

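### As described, adverse events are ascertained differently by arm and by attendance, so counts could not be compared between arms without bias

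*Protocol article*

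**What the plan says.** Four parts of the protocol article bear on how harms come to be recorded.

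- **Strategies for trial retention.** The team uses WhatsApp "messages to ask about adverse events if an IG participant misses a session". Two conditions must be met: being in the IG, and being absent. The same section says that messages stop once a participant declares withdrawal.
- **Harms.** "If adverse events are reported, they are collected and classified according to severity", as well as by predictability and relation to study procedures. The section adds that "The research team is available to solve any adverse events". It gives no time point and no standard question, and it does not distinguish the arms. Much of its practical content (a companion at home, emergency contacts, advice for the classes) concerns the exercise sessions.
- **Contact with each arm.** The IG trains under live video supervision, "with a maximum of 5 participants per video call", over thirty scheduled sessions (Remotely supervised exercise program; Adherence). Controls are sent chapters of a physical activity guide after baseline (Control group), and no further contact is described until the final evaluation.
- **Outcomes and Table 1.** Both arms are assessed at week 0 and week 13. Table 1 lists the assessments down to eating habits and well-being but has no adverse-event row.

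**The concern.** A count of adverse events reflects both how often events happen and how hard someone looks for them. Here the looking differs in two ways. It differs by arm, because the described prompt and the live supervision exist only in the IG. It also differs within the IG, because an absence triggers a question and attendance does not. A participant who has symptoms between sessions but still joins the next call is not described as being asked.

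Three consequences follow. A between-arm table of events would mix true risk with unequal detection. An IG-only count would have no equally ascertained background rate for people with type 2 diabetes. Events between sessions in regular attenders would be recorded only if volunteered. The article also states that there is no dedicated monitoring committee (Data monitoring and auditing), so what the trial can say about the safety of exercising at home depends on this collection.

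**Working it through.** The plan gives no figure on this point, so there is nothing to reproduce. The check has two parts: setting the text out by type of participant, then an illustration of size.

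**1. Described routes by which an event can be recorded**

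| Participant | Actively asked | Observed live | Volunteered |
|---|---|---|---|
| IG, missed a session | yes | no (for that session) | yes |
| IG, attending, event in a session | not described | yes | yes |
| IG, attending, event between sessions | not described | no | yes |
| Control | not described | no | yes |

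Only the last column is common to both arms.

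**2. How large the distortion could be**

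Inputs from the article: 50 randomised (Sample size), "in blocks of different sizes with a 1:1 ratio", hence 50/2 = 25 per arm; sessions 6 × 2 + 6 × 3 = 30, which agrees with the thirty given under Adherence.

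Assumed inputs (none is in the article):
- the same true risk *p* in both arms;
- *s*, the probability that an unprompted event is recorded, the same in both arms;
- *a*, the probability that a prompted event is recorded;
- *m*, the share of IG events linked to a missed session, and so prompted.

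Expected recorded proportions:
- IG: *p*[*m a* + (1 − *m*)*s*]
- Control: *p s*
- Apparent ratio: [*m a* + (1 − *m*)*s*]/*s* = 1 + *m*(*a* − *s*)/*s*

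The risk *p* cancels. The ratio exceeds 1 whenever prompting captures more than waiting for reports (*a* > *s*) and some events are prompted (*m* > 0).

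| *a* | *s* | ratio, *m* = 0.2 | ratio, *m* = 0.5 |
|---|---|---|---|
| 0.95 | 0.3 | 1.43 | 2.08 |
| 0.95 | 0.5 | 1.18 | 1.45 |
| 0.95 | 0.7 | 1.07 | 1.18 |
| 0.90 | 0.3 | 1.40 | 2.00 |
| 0.90 | 0.5 | 1.16 | 1.40 |

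Extremes, worked out:
- lowest: (0.2 × 0.95 + 0.8 × 0.7)/0.7 = 0.75/0.7 = 1.07
- highest: (0.5 × 0.95 + 0.5 × 0.3)/0.3 = 0.625/0.3 = 2.08

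In participants: if 40% of 25 (10 per arm) truly have an event, with *a* = 0.95 and *s* = *m* = 0.5, the expected recorded numbers are 10 × 0.725 = 7.25 in the IG and 10 × 0.5 = 5.0 in controls.

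The illustration leaves out live observation, which would raise capture in the IG only and widen the gap.

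**The case against.** The strongest reply is that this is a condensed article. It refers to a protocol dated December 2022 and says that the full protocol is available on request. Question wording and visit scripts usually sit there. The retention section does not claim to describe the whole harms system, and the Harms section does not rule out asking both arms at week 13. This stands against reading the article as saying that controls are never asked; that is an inference from silence. It does not remove the point. The article has its own Harms section and a full time scheme, it spells out one specific trigger, and that trigger is tied to arm and absence.

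Second, no between-arm comparison of harms is planned. Adverse events are not among the outcomes, and Statistical analyses does not mention them. This stands: the bias affects a comparison that might be made later, not a prespecified one.

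Third, attenders are watched live in small groups. This also stands. A reader might infer that events in regular attenders are not sought at all, but the gap is confined to events between sessions that participants do not volunteer.

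Fourth, the directions seem to conflict: extra detection in the IG makes exercise look worse, while missed events in attenders make it look safer. They concern different quantities. The absolute IG count is too low, but under equal unprompted capture the control count is too low by more, so the ratio is pushed above 1.

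A reader might also infer a larger effect, such as 30 prompts per IG participant against none per control, or a spurious ratio of 1.8 to 3. Neither is supported. Thirty prompts would require missing all 30 sessions. Ratios of 0.9/0.5 = 1.8 to 0.9/0.3 = 3.0 arise only if every IG event is prompted (*m* = 1), which contradicts a rule that asks absentees only.

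**Conclusion.** The point holds in limited form. As described, ascertainment of adverse events differs by arm and by attendance, and counts collected this way could not be compared between arms without bias, most plausibly against exercise. The size is unknown. An apparent ratio of roughly 1.1 to 2 under a true ratio of 1 rests wholly on assumed capture rates (0.90 to 0.95 prompted, 0.3 to 0.7 unprompted) and an assumed 20 to 50% of IG events linked to an absence. That no other enquiry exists is inferred from this article and should be checked against the full protocol.

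The stronger conclusion, that harms cannot be compared at all, does not follow. Volunteered control events can still be recorded, and a common question would permit a fair comparison. The primary HbA1c analysis is untouched. The point is worth acting on because the remedy is cheap and any later safety statement would depend on it.

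**What to change.** 1. Put one identical adverse-event question to all participants in both arms, regardless of attendance or withdrawal from sessions, in the existing week-13 assessment forms, and add the row to Table 1. Word it without reference to exercise sessions. Place it last in the online questionnaires, so that an answer cannot reveal the group to a blinded assessor before the outcomes are taken.
2. Base any between-arm harms table on this question alone. Report session-observed and absence-prompted IG events separately and descriptively, labelled by how they came to light.
3. If the week-13 visits are over, send everyone the same question once, retrospectively. This is likely to be needed for many participants. Recruitment ended in June 2023; 13 weeks from 30 June is 29 September, before the article's publication on 19 October 2023, if the last participants started promptly (an assumption). A new mid-study prompt would probably come too late. If only some week-13 visits remain, the question should not go to late enrollees alone.
4. If common ascertainment is no longer possible, state in the report that it was unequal and make no between-arm safety claim.

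Cost: one question in forms already in use, or one message to each participant, with notice to the ethics committee and a registry update as Protocol amendments requires. The downside is recall. Twelve weeks is a long period to remember minor events, and IG participants who were prompted or supervised may recall them somewhat better, so the bias is reduced but not removed.
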